### Strategies to improve adherence to interventions

All treatments will be administered to participants during their stay in the hospital by attending surgeons. Therefore participants’ adherence to interventions is assured.

### Relevant concomitant care permitted or prohibited during the trial

All other treatments will be allowed.

### Provisions for post-trial care

All patients who will suffer harm from trial participation will be covered by the Japanese public healthcare system.

### Clinical assessments

At entry, clinical research physicians obtain information from patients regarding age, sex, past history, medications, cause of SCI (traumatic or non-traumatic), level of SCI (cervical, thoracic, lumbar), location of pain (arm, leg, lower back, back, chest), degree of paralysis (none, mild, moderate, severe), sensory disturbance (hypoesthesia, allodynia, numbness), duration of disease, and Frankel grade (B-E). During the SCS trial, the degree of pain is evaluated using a VAS according to the plan (Table 1). After SCS system implantation, assessment items are evaluated according to the plan, including degree of improvement of pain relief, mental health, comprehensive health, and gait function (Table 1). Six months after SCS system implantation, if no improvement of any of the assessment items is seen, removal of the implanted SCS system would be considered.

**Table 1 Tab1:**
[figure not shown]
Summary of observations, assessment items, and schedule of assessments

*VAS* visual analog scale, *SF-MPQ-2* short-form McGill pain questionnaire-2, *PCS* pain catastrophizing scale, *QIDS-J* quick inventory of depressive symptomatology, *SF-36* short-form 36-item health survey, *FAC* functional ambulation categories, *MRI* magnetic resonance image, *Xp* X-ray picture, *CT* computed tomography, *SCS* spinal cord stimulation

### Assessment items

Assessments of pain relief are performed by a VAS and the short-form McGill pain questionnaire-2 (SF-MPQ-2). Assessments of mental health and comprehensive health are performed by the pain catastrophizing scale (PCS), quick inventory of depressive symptomatology (QIDS-J), and the Short-Form 36-item health survey (SF-36^®^). Assessment of gait function is performed by functional ambulation category (FAC).

### Imaging evaluation

The location of the spinal cord lesion is confirmed by magnetic resonance imaging (MRI) taken before the initial spinal surgery for SCI. Before the SCS trial, whole spinal MRI is performed to rule out any other abnormal findings, and whole spinal X-rays are also performed to confirm the location and type of fixation devices implanted in previous spinal surgeries. After the SCS trial and SCS system implantation, spinal X-rays and computed tomography (CT) are performed to confirm the location of the SCS leads and to rule out postoperative complications.

### Primary outcome

Pain improvement is defined as more than a 33% reduction in the VAS score. The primary outcome is rates of achieving pain improvement at 3 months after SCS system implantation.

### Secondary outcomes

The secondary outcomes are as follows: (1) evaluation of effectiveness of DTM and tonic stimulations in the SCS trial; (2) evaluation of changes of assessment scores, VAS, SF-MPQ-2, PCS, QIDS-J, and SF-36^®^, at 1, 3, 6, 12, 18, and 24 months from SCS system implantation; (3) relationship between the result of the SCS trial and the effect 3 months after SCS system implantation; (4) evaluation of preoperative factors associated with a long-term effect, defined as continuing for more than 12 months; (5) evaluation whether there is improvement of motor function using the gait function scale (FAC) at 1, 3, 6, 12, 18, and 24 months from SCS system implantation; and (6) adverse events related to this study 3 months after SCS system implantation.

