### Statistical analysis

The primary outcome will be estimated as the probability of patients achieving more than 33% pain improvement on the VAS at 3 months after SCS system implantation. The secondary outcome analyses are as follows:A logistic regression analysis using stimulation timing (Stim-1, Stim-2), stimulation pattern (tonic, DTM), pre-VAS values for each stimulation, and interaction between stimulation timing and stimulation pattern as explanatory variables. The carryover effect is examined by testing the interaction term at a significance level of 10%. If a carryover effect is observed, an additional analysis will be performed using only Stim-1.Adjusted means and 95% confidence intervals (CIs) of the rate of change or amount of change for each item (VAS, SF-MPQ-2, PCS, QIDS-J, and SF-36^®^) are calculated for each evaluation time point including pre-implantation and post 1, 3, 6, 12, 18, and 24 months using linear mixed models with time points as fixed effects. The amount of change of each item at each time point is compared after using the Dunnet-Hsu correction for multiple comparisons.For the patients undergoing implantation, logistic regression will be performed to investigate the relationship between the efficacy of the SCS trial (DTM) and the effectiveness for 33% improvement on the VAS at 3 months after implantation.Preoperative factors associated with long-term effects are examined using logistic regression analysis as explanatory variables for the following items: sex, age (<60 years vs. ≥60 years), disease duration, pain site (arm, leg, lower back, back, chest), level of SCI (cervical, thoracic, lumbar), paralysis (none, mild, moderate, severe), sensory disturbance (hypoesthesia, allodynia, numbness), and Frankel classification (B, C, D, E).Probability of gait improvement is estimated, defining an improvement as 1 point or more in the FAC category. The probability of improved cases and the 95% CIs will be calculated at each evaluation time point.

Safety analysis will be performed by tabulating the number and probability of each event.

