#### Adverse event reporting and harms

Researchers will immediately report serious adverse events associated with the trial to the chief investigator. Then, the chief investigator will report serious adverse events to the director of the hospital and the principal investigator. Data about all serious adverse events will also be collected in REDCap.

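### The only adverse-event outcome is set at 3 months after implantation while benefit is followed to 24 months, and the sections on safety are not reconciled

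*Protocol article*

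**What the plan says.** All six secondary outcomes stand in one list in the protocol article, under Secondary outcomes.

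- **Benefit.** The pain, mental-health and general-health scores are assessed "at 1, 3, 6, 12, 18, and 24 months from SCS system implantation". Gait is treated the same way: "improvement of motor function using the gait function scale (FAC) at 1, 3, 6, 12, 18, and 24 months". A further item looks for "preoperative factors associated with a long-term effect, defined as continuing for more than 12 months".
- **Harm.** The sixth and last item is "6) adverse events related to this study 3 months after SCS system implantation". No other adverse-event outcome is defined.

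Three other sections bear on the point.

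- **Clinical assessments:** at six months, if no assessment item has improved, "removal of the implanted SCS system would be considered".
- **Statistical analysis:** "Safety analysis will be performed by tabulating the number and probability of each event". No period is given.
- **Adverse event reporting and harms:** "Data about all serious adverse events will also be collected in REDCap". No period is given here either, and the sentence covers serious events only.

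**The concern.** The intervention is a paddle lead placed by laminectomy and connected to an implanted pulse generator. Both remain in the patient after month 3, so exposure to device problems continues through the whole period over which benefit is estimated. The article itself foresees that some systems may be removed after six months, which is later than its adverse-event outcome reaches.

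What is at stake is the benefit-risk account of a long-term implant. As defined, the outcomes would set benefit at up to 24 months beside harm at 3 months. Late lead failure or migration that does not qualify as serious has no defined place in the results, and neither has a revision or removal. If such events are not recorded as they occur, they cannot be fully recovered afterwards.

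The point concerns the late end of the window only. It does not concern the SCS-trial step or patients who are never implanted.

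**Working it through.** The article gives no figure for device complications, so there is nothing of its own to reproduce. The check has two parts.

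**1. Windows side by side**

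| Item | Section | Period after implantation |
|---|---|---|
| Pain and health scores | Secondary outcomes, item 2 | 1 to 24 months |
| Gait (FAC) | Secondary outcomes, item 5 | 1 to 24 months |
| Long-term effect | Secondary outcomes, item 4 | more than 12 months |
| Adverse events | Secondary outcomes, item 6 | 3 months |
| Possible removal | Clinical assessments | considered at 6 months |
| Tabulation of events | Statistical analysis | not stated |
| Serious adverse events | Adverse event reporting and harms | not stated |

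Item 6 is read here as events up to month 3.

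- Share of follow-up covered: 3/24 = 12.5%, leaving 21/24 = 87.5% outside.
- With 10 implanted patients: 10 × 3 = 30 of 10 × 24 = 240 patient-months. The 240 is a ceiling. Study procedures makes implantation conditional, and removals or withdrawals would shorten exposure.

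The planned safety table reports a probability, and a probability needs a risk period. The only adverse-event period in the article is the 3 months in item 6.

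**2. Illustration of size**

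The sample size of 10 is from the article, and it is assumed that all 10 are implanted. Also assumed are a 24-month risk R of a first device-related event of 20% (range 10% to 40%) and a constant hazard. Then:

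- 3-month risk = 1 − (1 − R)^(3/24)
- expected patients with an event = 10 × risk
- chance of no event among 10 = (1 − risk)^10

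| R at 24 months | Risk at 3 months | Expected patients, 3 vs 24 months | Chance of no event, 3 vs 24 months |
|---|---|---|---|
| 10% | 1.3% | 0.13 vs 1.0 | 88% vs 35% |
| 20% | 2.7% | 0.28 vs 2.0 | 76% vs 11% |
| 40% | 6.2% | 0.62 vs 4.0 | 53% vs 0.6% |

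Under these assumptions the 3-month window misses about 84% to 87% of the patients who have a first event by month 24.

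Two sensitivities at R = 20%:

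- With only 5 patients implanted, the comparison is 0.14 against 1.0.
- If half of the affected patients had their first event within 3 months, because events cluster around surgery, the 3-month window would capture 0.5 × 2.0 = 1.0 of the 2.0. Late clustering would widen the gap.

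**The case against.** The strongest objection is that late harm is not shut out. Serious adverse events go into REDCap with no end date, and the planned tabulation of each event is tied to no window. A reader might infer from item 6 that late complications never enter the reported risk. The article does not say so: no section states that safety collection or tabulation stops at month 3. This part of the objection stands. It does not close the gap, because the open-ended collection is stated for serious events only, and collecting an event is not the same as reporting it under a defined outcome.

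A reader might also take removal at six months as planned surgery that the safety outcome ignores. The text makes it conditional on no improvement and says only that it would be considered. A removal for lack of effect is not necessarily an adverse event. This too stands, and it is why removals need their own line and should not be counted automatically as harm.

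The 3-month point has a rationale, since it matches the primary outcome and the third secondary outcome. That is a good reason to keep a 3-month figure, but not to have it as the only one in a trial that also estimates 24-month benefit.

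Table 1, which holds the assessment schedule, is not visible in the text at hand. It may already schedule adverse-event recording at the later visits. If so, the recording part of the fix is unnecessary, but the wording of item 6 would still need to change.

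Finally, a 3-month probability is not biased low. It is a valid shorter-term quantity, and would mislead only if presented as the risk over 24 months, which the article does not propose.

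**Conclusion.** The point holds as a mismatch of windows. The one defined adverse-event outcome ends at 3 months, covering 12.5% of the follow-up over which benefit is estimated. It is not reconciled with two sections on safety that state no limit. The exposed part is late non-serious device events, together with revisions and removals; late serious events may well be captured.

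The 12.5% follows from the article alone. The contrast of 0.28 with 2.0 expected patients is illustrative. It rests on an assumed 20% risk, a constant hazard and full implantation of 10 patients, and early clustering would make it smaller.

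This should be fixed, but it is not critical. The trial is exploratory with 10 patients, the primary outcome and the efficacy analyses are unaffected, and serious-event reporting is not shown to lapse.

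**What to change.** 1. Restate the sixth secondary outcome as adverse events from implantation through the 24-month visit.
2. Tabulate patients with each event cumulatively at 3 months, matching the primary time point, and at 24 months, with patient-months of exposure.
3. Make the safety sentence in Statistical analysis and the collection sentence in Adverse event reporting and harms refer to that window, without narrowing the present open-ended collection of serious events.
4. Report device revisions and removals, with reasons, as a separate item.
5. Record events at the existing 6, 12, 18 and 24 month visits, if Table 1 does not already provide for this.

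The cost is small: a reworded outcome line, two cross-references, and up to four more data entries per patient in REDCap. The full safety table becomes available only at the end of follow-up, but the 3-month table can still accompany the primary result. No clinical rule changes.

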**Fig. 1 Fig1:**
[figure not shown]
The order of stimulation patterns. The order of stimulation patterns of DTM or tonic is randomly assigned to two courses. One course is DTM stimulation (Stim-1), then tonic stimulation (Stim-2). The other course is in reverse order. Each stimulation pattern is performed for two days. The stimulation off period is set as one day between Stim-1 and Stim-2 (Stim-off)

After the SCS trial, the inserted leads are removed whether or not analgesic effects are obtained. In cases of an effective SCS trial or the patient agrees to implantation of an SCS system even after a non-effective SCS trial, the second step follows. With an interval of 1 month from the SCS trial, a paddle-type lead is placed on the rostral side of the SCI by laminectomy under general anesthesia (Fig. 2). The location of the lead is confirmed by intraoperative X-ray and motor-evoked potential monitoring. At the same time, an implantable pulse generator (IPG) (Intellis; Medtronic Inc.) is implanted on the hip, and it is connected to the paddle-type lead. After the SCS implantation, an effective stimulation pattern that showed efficacy in the SCS trial is started, and the analgesic effects are evaluated. In the absence of analgesic effects in the previous SCS trial, DTM stimulation is tried.

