### Sample size

There is no reference clinical data for the efficacy of DTM stimulation using a paddle-type lead placed on the rostral side of the SCI because there is only one case report [26]. Therefore, the sample size is not able to determine on statistical assumptions. Assume that there are 2 to 4 cases who meet the inclusion criteria of this study in a year. The sample size is set 10 as the number that can be achieved in 3 to 5 years.

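### The adverse-event outcome is defined only to 3 months after implantation, while benefit is reported to 24 months and the safety analysis states no time window

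*Protocol article*

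**What the plan says.** Secondary outcomes lists six items. Item (6), the only one on safety, is "adverse events related to this study 3 months after SCS system implantation". Item (2), on the pain, mental-health and quality-of-life scores, and item (5), on gait, are both assessed "at 1, 3, 6, 12, 18, and 24 months from SCS system implantation". Item (4) is the "evaluation of preoperative factors associated with a long-term effect, defined as continuing for more than 12 months".

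The intervention is a paddle lead placed by laminectomy under general anesthesia, and in the same operation "an implantable pulse generator (IPG) (Intellis; Medtronic Inc.) is implanted on the hip, and it is connected to the paddle-type lead" (Study procedures). Under Clinical assessments, if nothing has improved six months after implantation, "removal of the implanted SCS system would be considered".

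Two other statements bear on harms. Statistical analysis says "Safety analysis will be performed by tabulating the number and probability of each event" and gives no period. Adverse event reporting and harms says "Data about all serious adverse events will also be collected in REDCap" and gives no end date.

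**The concern.** Three months is the only time limit the article attaches to an adverse-event outcome, and no section extends it. Whether item (6) means events present at month 3 or events occurring up to month 3, it stops there. Patients then carry the implant through a further 21 months of planned follow-up, in which efficacy outcomes are defined and safety outcomes are not.

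Two things are at stake. First, a report that follows the outcome list would describe benefit over 24 months and harm over 3, so the long-term benefit results would have no harm results beside them from the same period. Second, the safety analysis promises a probability for each event. A probability needs a period and a denominator. Secondary outcomes gives a period of 3 months, Statistical analysis gives none, and an analyst could reasonably follow either.

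**Working it through.** The plan gives no event rate or safety precision figure to reproduce. The check is a comparison of sections, one ratio and an illustration on assumed risks.

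**Sections side by side**

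| Item | Place in the Protocol article | Time frame |
|---|---|---|
| Adverse-event outcome (6) | Secondary outcomes | 3 months after implantation |
| Score outcomes (2) | Secondary outcomes | 1 to 24 months |
| Long-term effect (4) | Secondary outcomes | more than 12 months |
| Gait outcome (5) | Secondary outcomes | 1 to 24 months |
| Safety tabulation | Statistical analysis | none stated |
| Serious adverse events in the database | Adverse event reporting and harms | no end date stated |

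**Share of follow-up covered**

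- Covered: 3 / 24 = 12.5%.
- Not covered: 24 − 3 = 21 months, and 21 / 24 = 87.5%.

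These are shares of calendar time, not of risk.

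**Illustration of what the window could mean**

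The document gives no device-event risk, so the 24-month risk R is assumed to lie between 10% and 40%. Also assumed: a constant hazard, and all 10 planned patients implanted and followed. The figure of 10 comes from Sample size: "The sample size is set 10 as the number that can be achieved in 3 to 5 years".

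- Hazard per month: h = −ln(1 − R) / 24.
- Risk by 3 months: p3 = 1 − exp(−3h) = 1 − (1 − R)^(1/8).
- Share of first events inside 3 months: p3 / R.
- Chance of at least one patient with an event among 10: 1 − (1 − p)^10, with p = p3 or p = R.

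| R (assumed) | p3 | Share inside 3 months | At least one in 10, to 3 months | At least one in 10, to 24 months |
|---|---|---|---|---|
| 10% | 1.31% | 13.1% | 12.3% | 65.1% |
| 20% | 2.75% | 13.8% | 24.3% | 89.3% |
| 30% | 4.36% | 14.5% | 36.0% | 97.2% |
| 40% | 6.19% | 15.5% | 47.2% | 99.4% |

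For R = 10%, for example: p3 = 1 − 0.9^(1/8) = 0.0131, the share is 0.0131 / 0.10 = 13.1%, and 1 − (1 − 0.0131)^10 = 12.3%, against 1 − 0.9^10 = 65.1%.

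Under a constant hazard, about 13% to 16% of first events by month 24 would fall inside the outcome as defined. Events clustered around the operation would have a larger share inside the window and late device problems a smaller one. The table shows direction and rough scale and is not a forecast for this device.

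**The case against.** The strongest reply is that nothing in the article says later events are ignored. Serious adverse events are recorded without an end date, and the safety tabulation has no 3-month limit. Table 1, the assessment schedule, is not visible in the text at hand. The article also condenses a fuller protocol, where collection periods for non-serious events commonly sit. All of this stands. A reader might infer that late harms will go uncollected or be discarded, and the documents do not support that. The point concerns the defined outcome, not data capture.

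A reader might also infer that removals at six months are safety events the plan misses. That goes too far. Removal is only to be considered, and the trigger is lack of improvement, not harm. A complication of such an operation would be a harm, and a serious one would come under the general reporting rule.

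Events during the SCS trial phase might seem excluded because the clock starts at implantation. But item (6) covers events related to the study, and the study includes both steps, so those events can be read as included. The wording needs tightening here; an exclusion is not shown.

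Finally, the primary outcome is also at 3 months and the trial is labelled exploratory, so the main benefit and safety outcomes do share a time point. That answers any charge that the whole benefit-risk comparison is one-sided. It does not answer the mismatch for items (2), (4) and (5), which are the long-term claims.

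**Conclusion.** The point holds as a mismatch between defined outcomes. Item (6) limits the adverse-event outcome to 3 of the 24 months over which benefit is reported, for an implant placed by laminectomy that stays in the patient, and the safety analysis does not state the same window. This is a stated rule and not a detail left to another document. Serious events may well be captured after month 3, but no safety outcome is defined for them.

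The firm figures are the 12.5% covered and the 21 months not covered, which follow directly from the article. The 13% to 16% share of first events rests on an assumed constant hazard and assumed 24-month risks of 10% to 40%. The chances of seeing at least one event also assume that all 10 patients are implanted, although Study procedures makes implantation conditional. The conclusion does not depend on the illustration. The change is worth making before reporting, because it is cheap and lets benefit and harm be read over the same period.

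**What to change.** - Define item (6) as adverse events from insertion of the trial leads through the 24-month visit, and keep the 3-month result as one row of the table.
- Tabulate the SCS trial phase separately, with patients who had leads in place as the denominator.
- List any surgical revision or system removal separately, with its reason (lack of effect or harm), so that a removal for lack of effect is not counted as an adverse event. This concerns reporting only and leaves the removal provision as it is.
- Do not count reprogramming as a device event: the section on participant retention books SCS adjustments for all patients.
- State the same window in Secondary outcomes and in the safety paragraph of Statistical analysis.

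The cost is a small amount of data entry at the 6-, 12-, 18- and 24-month visits, which are already scheduled. No extra visits or patients are needed.
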